### Sample size calculation

The sample size was calculated using free-to use software, namely G*Power for Windows V.3.1.9.6.^33^ The effect size is 0.81, type 1 error (α)=5% (two-tailed), power (1−β) 90% and the allocation ratio between the groups is 1:1. The effect size was set with reference to previous studies with similar outcomes.^9^ According to the G*Power calculation, the study sample size should be 34 per group. With consideration of an expected dropout rate of 15%, the sample size was increased to 40 per group.

The participant dropout criteria are as follows:

The patient being unwilling to continue the sequence of the study process (lost to follow-up).The patients experiencing drug extravasation incidents or severe side effects during chemotherapy.

The consecutive sampling technique will be applied. This non-probability sampling method involves recruiting all individuals from the accessible population during a given time interval or for a specific sample size. Patients with cancer who have scheduled chemotherapy and meet the requirements of the data collection time will be asked to participate in the study.

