### Participant characteristics and study outcomes

#### Participant characteristics

A questionnaire will be used to collect patient demographic data, including age, sex, education level, marital status, occupation, income and assistance during chemotherapy, and clinical characteristics, including the type of cancer, body surface area (height and weight), cancer stage, duration of diagnosis, chemotherapy cycle and ECOG Score.

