Anxiety is measured using the Visual Analogue Scale for Anxiety (VAS-A) in the form of a horizontal line with a scale of 100 mm or 10 cm, with the left by the words ‘not at all anxious’ and on the right by ‘extremely anxious’.^36 37^ VAS-A has a sensitivity of 76.8%, specifications of 64.9% and internal reliability consistency (Cronbach’s α ≥0.7).^36 37^

Pain is measured using the Numerical Rating Scale (NRS). The NRS consists of numerical scale; from 0 to 100 (101-point scale), 0 to 10 (11-point scale) or 1 to 10 (10-point scale). This study will use a 0–10 NRS due to it provides more sufficient sensitivity to measure pain in most patients with cancer.^38^ The NRS has been declared valid and reliable for subjective measurement of cancer pain, both due to adverse effects of cytotoxic agents, cancer treatment procedures (surgery, radiotherapy and chemotherapy) and the malignancy of the cancer itself.^39^

Pulse rate and blood pressure (systolic and diastolic pressure) are measured using an automatic digital sphygmomanometer. According to American Heart Association, the regular resting heart rate for adults is 60–100 beats per minute, and systolic blood pressure is above 90 mm Hg and less than 120 mm Hg, with a diastolic pressure between 60 mm Hg and less than 80 mm Hg.^40^

Comfort and self-efficacy for symptom management will be measured at two time points: at baseline (before chemotherapy premedication) and post-test (after the chemotherapy session is completed). Anxiety, pain and vital signs (pulse rate and blood pressure) will be measured at five time points: thrice at pretest (baseline data collection, before the installation of intravenous access and before administration of VR intervention) and twice at post-test (immediately after intervention and after the chemotherapy session is completed). The timeline of the data collection and measurement is presented in table 2.

**Table 2 T2:** Timeline of data collection and measurements

Assessment/measurement instrument	Study period				
	T0	T1	T2	T3	T4
Demographic variables	**X**				
Clinical characteristics	**X**				
SGCQ	**X**				**X**
SE-CSSMS	**X**				**X**
VAS-A	**X**	**X**	**X**	**X**	**X**
NPRS	**X**	**X**	**X**	**X**	**X**
Blood pressure	**X**	**X**	**X**	**X**	**X**
Pulse rate	**X**	**X**	**X**	**X**	**X**

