### Data analysis

The collected data will be processed using IBM SPSS statistical software V.23 for Windows through editing, coding and data entry processes. The statistician will be blinded to the study outcomes and will conduct analyses on the basis of the labelling of the groups. For the treatment group, the demographic and clinical variables recorded at enrolment will be tabulated. The descriptive statistics will be presented as numbers, means, SDs, medians, minimums and maximums. Homogeneity and normality tests will be conducted before the bivariate analysis test. A homogeneity test for categorical data (age, sex, education level, marital status, occupation, income, the presence of a family member or caregiver during chemotherapy, type of cancer, stage of cancer, duration of cancer diagnosis, chemotherapy cycle and ECOG Scores) will be performed using the χ^2^ test or Fisher’s test, whereas a homogeneity test for numerical data (height and weight) will be performed using Levene’s test if the data are normally distributed and using the Mann-Whitney U test if the data are not normally distributed. Both groups will be considered to be homogeneous if p>0.05. Bivariate analysis will be used to determine the differences in the mean scores for comfort level and symptom management self-efficacy before and after treatment in the intervention and control groups. If the data distribution is normal, we will use a paired t-test and independent t-test. However, if the data distribution is not normal, the non-parametric Wilcoxon and Mann-Whitney U tests will be used if significant differences are identified (p<0.05). For anxiety, pain and vital-sign (blood pressure and pulse rate) outcome measurement analysis, General Linear Model-Repeated Measure (GLM-RM) statistics will be used. The GLM-RM is a statistical test used for the comparative analysis of two unpaired numerical data groups with more than two measurements and is applied when the effect of a treatment or intervention is measured at different time points. If the data are not normally distributed, the repeated Mann-Whitney alternative test with Bonferroni correction will be used. The present study will use statistical method to adjust for potentially confounding effects of the S-VR intervention on the patient’s outcomes. These confounders include age, gender, education, cancer stage, chemotherapy cycle, assistance during chemotherapy and comorbidities. Multivariate model can handle identified confounders and minimise the bias effect of the intervention.^45^ Linear regression analysis will be applied by using the enter method. Adjustment by using this analysis can clarify that how much the confounders in the model distort the intervention and outcome.^46^

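### The between-arm comfort test is not fixed (T4 score or change, t-test or Mann-Whitney), and no stated analysis adjusts it for the baseline SGCQ score that the trial collects

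*Protocol article*

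**What the plan says.** All references are to the protocol article.

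- **Timing (Outcomes).** "Comfort and self-efficacy for symptom management will be measured at two time points: at baseline (before chemotherapy premedication") and again after the chemotherapy session. Table 2 labels these T0 and T4.
- **Hypothesis (end of the Introduction).** Comfort is expected to improve more with S-VR than in the control group. This is a between-arm statement about improvement.
- **Tests for comfort and self-efficacy (Data analysis).** "If the data distribution is normal, we will use a paired t-test and independent t-test". If the distribution is not normal, "the non-parametric Wilcoxon and Mann-Whitney U tests will be used if significant differences are identified (p<0.05").
- **Adjusted model (Data analysis).** A linear regression with all covariates entered together is planned. On the covariates: "These confounders include age, gender, education, cancer stage, chemotherapy cycle, assistance during chemotherapy and comorbidities". T0 SGCQ is not named, and the section does not say whether this regression or the bivariate test decides the trial.
- **Baseline comparability (Data analysis).** "a homogeneity test for numerical data (height and weight) will be performed using Levene’s test if the data are normally distributed"; p above 0.05 is read as homogeneity.
- **Sample size.** "The effect size is 0.81, type 1 error (α)=5% (two-tailed), power (1−β) 90% and the allocation ratio between the groups is 1:1", giving 34 per group, raised to 40 for 15% dropout.

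**The concern.** Three things about the primary comparison are left loose or left out.

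1. **The outcome variable.** An independent t-test can be run on T4 scores or on change from T0. The two have different variances, and they respond in opposite directions to a chance baseline gap.
2. **The test.** A normality result chooses between a t-test, which goes with a mean difference, and a Mann-Whitney test, which goes with a rank shift. What the trial estimates then depends on the data. The added condition about significant differences is unclear: read literally, a test would be selected by a test result.
3. **The baseline score.** T0 SGCQ is likely to be among the best available predictors of T4 SGCQ, yet it is not a named covariate. Allocation is by simple randomisation, so nothing in the design balances T0 comfort between arms.

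The paired tests do not fill the gap. Each asks whether comfort changed within one arm, and a significant change in one arm but not in the other is not a test of the difference between arms. At stake are the precision of the primary estimate and the clarity of which result is the trial's answer.

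**Working it through.** **Inputs.** From Sample size calculation: d = 0.81, two-sided α = 0.05, power 90%, ratio 1:1, 34 per group before dropout. The T0–T4 correlation r is not in the documents; 0.3, 0.5 and 0.7 are assumed. The SGCQ SD is assumed equal at T0 and T4, and d is taken on the T4 SD.

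**Step 1: the plan's own figure.** For a two-sample t-test with n per arm, the noncentrality is d·√(n/2) on 2n − 2 degrees of freedom. At n = 34 it is 0.81 × √17 = 3.34 on 66 df, and power is 0.908. At n = 33 power is 0.8998, just short. So 34 reproduces, and 34/0.85 = 40.

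**Step 2: power under each analysis.** The variance relative to a T4 comparison is 1 for T4 scores, 2(1 − r) for change scores, and 1 − r² for ANCOVA. The effective d is 0.81 divided by the square root of that factor. ANCOVA loses one further degree of freedom (65).

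| r (assumed) | Variance factor, change | Variance factor, ANCOVA | Power, T4 | Power, change | Power, ANCOVA | n per arm for 90%, ANCOVA |
|---|---|---|---|---|---|---|
| 0.3 | 1.40 | 0.91 | 90.8% | 79.4% | 93.2% | 31 |
| 0.5 | 1.00 | 0.75 | 90.8% | 90.8% | 96.7% | 26 |
| 0.7 | 0.60 | 0.51 | 90.8% | 98.9% | 99.6% | 18 |

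Relative to T4 scores, ANCOVA removes r² of the variance: 9%, 25% and 49%. Relative to change scores it removes (1 − r)/2: 35%, 25% and 15%.

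If the true effect were smaller, say d = 0.5 (an assumption, not a plan figure), power at 34 per arm would be 52.9% on T4 scores and 56.7%, 65.0% or 81.2% with ANCOVA.

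**Step 3: chance baseline imbalance.** The standard error of the T0 difference between arms, in SD units, is √(2/34) = 0.243. A gap of one SE shifts the T4 estimate by r × 0.243 and the change estimate by (r − 1) × 0.243.

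| r (assumed) | Shift in T4 estimate | Shift in change estimate |
|---|---|---|
| 0.3 | +0.07 SD | −0.17 SD |
| 0.5 | +0.12 SD | −0.12 SD |
| 0.7 | +0.17 SD | −0.07 SD |

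T4 scores under-correct and change scores over-correct. Regression on T0 removes the shift under a linear relation.

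**Step 4: the normality switch.** The procedure was simulated at 34 per arm with 20,000 runs per scenario: Shapiro-Wilk in each arm, then a t-test or Mann-Whitney. The type I error was 0.050 for normal data and 0.049 for skewed (gamma) data. No inflation appears in these scenarios. The cost of the switch is that the test and the estimand are not fixed.

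**The case against.** **Baseline is used.** A reader might infer that the comfort analysis ignores T0 altogether. The documents do not support that. The paired tests use T0 within each arm. The before-and-after wording, together with a hypothesis about improvement, also makes a change-score t-test a natural reading, which would bring T0 into the between-arm contrast. The point is narrower: the protocol does not say which variable is compared, and neither choice is a regression adjustment for T0.

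**The unadjusted test is valid.** Under randomisation the t-test's standard error already allows for chance imbalance, and only r times a T0 gap reaches a T4 comparison. This stands. The loss is of precision and of correction for the imbalance actually seen, not of validity.

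**The sample size is met.** On T4 scores the stated 90% holds at any correlation, and on change scores it holds once r is about 0.5 or more. The 79% figure belongs to change scores at r = 0.3 only. This also stands.

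**The covariate list is open-ended.** It is worded as including certain items, so T0 SGCQ is unnamed rather than excluded, and a fuller plan might add it. But the article itself fixes the tests, the switching rule and seven covariates, so the gap lies in what is written.

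**The odd p<0.05 clause** may be a misplaced statement of the significance level. It is best called unclear, not shown to be circular.

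**Comorbidities.** A reader might infer that the model uses a covariate that is never collected. The Participant characteristics section lists "clinical characteristics, including the type of cancer, body surface area (height and weight), cancer stage, duration of diagnosis, chemotherapy cycle and ECOG Score", but that list is introduced as non-exhaustive and medical records are reviewed, so this is not established.

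**Conclusion.** The point holds as a matter of precision and pre-specification. No between-arm comfort analysis is stated to adjust for T0 SGCQ, the between-arm variable is not fixed, and a normality result picks the test.

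At d = 0.81 and 34 per arm, for assumed r from 0.3 to 0.7, ANCOVA would gain about 2 to 9 percentage points of power over T4 scores. Over change scores it would gain about 14 points at r = 0.3, falling to under 1 at r = 0.7. A one-SE baseline gap would move the unadjusted estimate by 0.07 to 0.17 SD, in opposite directions for the two choices. These sizes rest on the assumed correlation and on equal SDs at T0 and T4.

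Two stronger readings are not supported. The sample size is not undermined, since 34 and 40 per arm reproduce. The power loss comes from the missing adjustment, not from the normality tests, which showed no type I error inflation in simulation.

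The use of Levene's test is a minor matter. It compares variances and so cannot show that mean height or weight is comparable, but neither variable enters any stated comfort analysis.

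**What to change.** Name one primary analysis before group-level data are seen, with no normality test in its path: a linear model of T4 SGCQ on arm with T0 SGCQ as covariate, reporting the adjusted mean difference and its 95% CI. Use the same model for SE-CSSMS, which is measured at the same two times.

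As sensitivity analyses, keep a rank-based or bootstrap version and the model with the further listed covariates. Holding those covariates out of the primary model avoids spending degrees of freedom that the power figures above do not count. Present the within-arm paired tests as descriptive only, and delete or reword the clause that makes the non-parametric tests conditional on significant differences.

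As a minor change, do not use Levene's test to declare height and weight comparable; show baseline summaries by arm, including the T0 outcome scores.

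The cost is wording only. T0 SGCQ and T0 SE-CSSMS are already collected, and the primary model spends one extra degree of freedom.

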T0: baseline data collection (after prechemotherapy assessment and obtaining signed informed consent); T1: before intravenous installation/premedication; T2: before the start of the intervention; T3: immediately after the intervention; T4: after completion of one chemotherapy cycle.

NPRS, Numerical Pain Rating Scale; SE-CSSMS, Self-Efficacy of Cancer Symptom Self-Management Scale; SGCQ, Shortened General Comfort Questionnaire; VAS-A, Visual Analogue Scale for Anxiety.

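### For anxiety, pain, blood pressure and pulse, GLM-RM by default drops any patient missing one of five readings, so up to 12 of 80 valid T3 readings could be lost and the T3 effect biased in either direction

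*Protocol article*

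**What the plan says.** All places are in the protocol article.

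- **Outcomes, schedule:** "Anxiety, pain and vital signs (pulse rate and blood pressure) will be measured at five time points". Three come before the intervention and two after it: "twice at post-test (immediately after intervention and after the chemotherapy session is completed". The legend to Table 2 has "T3: immediately after the intervention; T4: after completion of one chemotherapy cycle".
- **Data analysis, method:** "For anxiety, pain and vital-sign (blood pressure and pulse rate) outcome measurement analysis, General Linear Model-Repeated Measure (GLM-RM) statistics will be used". For software: "The collected data will be processed using IBM SPSS statistical software V.23 for Windows". If the data are not normal, "the repeated Mann-Whitney alternative test with Bonferroni correction will be used".
- **Sample size calculation, dropout:** "With consideration of an expected dropout rate of 15%, the sample size was increased to 40 per group". There are two dropout criteria. One is unwillingness to continue. The other is "The patients experiencing drug extravasation incidents or severe side effects during chemotherapy".

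The article does not state a complete-case rule, imputation, or the analysis set for these outcomes.

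**The concern.** GLM repeated measures in SPSS takes one row per patient, with the five readings as five columns. Its default is to exclude the whole row if one column is empty. The dropout criteria describe events that can happen during the infusion. The intervention lasts about ten minutes and T3 follows at once, so some of these events can fall between T3 and T4. Such a patient may have four valid readings per outcome, including the one closest to the intervention, and all four would go unused.

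Two things are at stake. One is precision at T3. The other is selection: at T3 the randomised comparison may still be nearly complete, but restricting it to patients who also reach T4 conditions on what happened later. Extravasation, severe side effects and unwillingness are plausibly related to pain, anxiety and vital signs, so this selection need not be neutral.

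**Working it through.** **1. The plan's own figure.** Inputs from Sample size calculation: d = 0.81, two-sided alpha 5%, power 90%, ratio 1:1. The exact two-sample t-test gives power 0.8998 at 33 per group and 0.908 at 34, so 34 is right. Inflation: 34/(1 - 0.15) = 40 per group. Both figures reproduce.

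**2. T3 readings discarded.** GLM-RM keeps 40 × 0.85 = 34 per arm. Let s be the share of dropouts who leave after T3. T3 readings taken per arm are 40 × (1 - 0.15 × (1 - s)), the excess over 34 is what is discarded, and the SE ratio is sqrt(T3 taken/34). The article does not give s, so the full range is shown. Power is for a simple two-group T3 comparison using all T3 readings; with the 34 completers it is 0.908.

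| s (assumed) | T3 taken per arm | Discarded per arm (of 80 in total) | SE ratio | Power at d = 0.81, all T3 readings |
|---|---|---|---|---|
| 0 | 34 | 0 (0) | 1.000 | 0.908 |
| 0.5 | 37 | 3 (6) | sqrt(37/34) = 1.043 | 0.930 |
| 1 | 40 | 6 (12) | sqrt(40/34) = 1.085 | 0.947 |

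The 0.81 was set for the trial's sample size, not for these outcomes. At an assumed d = 0.5 the power is 0.53 with completers and at most 0.60 with all T3 readings.

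**3. Bias at T3.** Assumptions, none of them from the article: true effect -0.50 SD, all dropout after T3, and probability of dropout logistic in the T3 value. The estimate from all T3 readings is -0.50 in every row.

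| Assumed mechanism | Completer estimate at T3 |
|---|---|
| Random, 15% in both arms | -0.50 |
| Slope 1.5 per SD, intercepts set to give 20% S-VR, 10% control | -0.60 |
| Same, slope 0.5 | -0.55 |
| Slope 1.5, intercepts set to give 25% S-VR, 5% control | -0.71 |
| Slope 1.5, intercepts set to give 15% in each arm | -0.50 |
| One common mechanism in both arms, slope 1.5, 15% overall | -0.42 |
| Slope 1.5 in S-VR only, random in control; rates 13% and 14% | -0.66 |

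The estimate can be exaggerated or attenuated. The last row shows bias with nearly equal dropout rates.

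**4. Bias at T4.** With within-patient correlation 0.6 (assumed) and slope 1.5, completers give -0.56 (20%/10%) and -0.63 (25%/5%). A likelihood-based model using all readings gives -0.50 in both.

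**5. Scattered gaps.** At an assumed 3% missing independently at each time point, 0.97^5 = 0.86 of patients have all five readings, about 34 of 40 per arm, before any dropout.

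**The case against.** The best defence is that the article names a procedure, not a missing-data rule. Imputation before GLM-RM would be compatible with the text, and an analysis plan that is not shown may provide it. This stands as a limit. A reader might infer that the plan prescribes a completer analysis; it does not. Exclusion is the default of the procedure the article fixes. The point is therefore about the choice of method, and a missing-data section is not being asked for.

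Further points stand in part:

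- **Twelve lost T3 readings is an upper bound.** Unwillingness or extravasation can occur before T3, when there is no T3 reading to lose. The readings all belong to one session and a research assistant accompanies participants to the room, so heavy loss between T3 and T4 is not an obvious expectation. The 34 completers per arm are also what the plan budgeted for.
- **The bias mechanisms are illustrations.** A reader might infer that completer analysis flatters S-VR, or that equal dropout rates make it safe. The calculations support neither as a general statement.
- **The fallback may or may not use different patients.** A reader might infer that the Mann-Whitney branch analyses everyone present at each time, so that a normality test decides who is analysed. That follows only if the tests are run per time point on available data, which the article does not say. If patients who meet the dropout criteria are removed from all analyses, both branches use the same patients, and changing the model alone would recover nothing.
- **The planned confounder-adjusted linear regression**, if run at T3, would not need all five readings. The article does not say which outcomes or time points it covers.

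**Conclusion.** The concern holds as a limited point about secondary outcomes. The article pairs five-time-point outcomes with a procedure that by default excludes incomplete patients, and its dropout criteria can be met after T3. At 15% dropout the cost is 0 to 12 of 80 valid T3 readings. The T3 standard error is up to 8.5% larger, and power at d = 0.81 is 0.908 instead of at most 0.947. This loss of precision is modest. The bias could matter more, but it depends on dropout being related to the T3 value: about -0.42 to -0.71 for a true -0.50 SD under mechanisms assumed here, with all dropout placed after T3. Random dropout gives no bias.

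A reader might take this as a threat to the main result. It is not: comfort is measured only at T0 and T4 and is analysed differently, and its sample size reproduces. The change is a cheap improvement.

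**What to change.** For anxiety, pain, blood pressure and pulse, replace GLM-RM with a linear mixed model for repeated measures (the MIXED procedure in SPSS). Include arm, time and arm-by-time, use an unstructured covariance, and fit by REML. State that every randomised patient contributes all readings taken, including those before dropout; without that sentence the change of model may recover nothing. Use the same all-available set for any non-parametric analysis, so that the normality result cannot alter who is analysed.

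The cost is a sentence or two in Data analysis and a different procedure in the same software, with no extra data. The downside is small: the model relies on dropout being explained by readings already observed (missing at random), which is a weaker assumption than completer analysis needs.

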### Patient recruitment

Recruitment will be conducted from April to July 2023. Patients who are scheduled for chemotherapy will be assessed by the nurse on duty, who will review their latest laboratory results, medical records, vital signs and ECG results, to determine whether they are eligible to undergo chemotherapy. The patients who pass the screening process will be asked whether they are willing to be involved in the study and will be asked to sign the informed consent form. Patients who are willing and who sign the informed consent form will be given a sealed envelope containing a random number indicating their group allocation. The participants will be evaluated (pretest) by the outcome assessor (research nurse) before they enter the chemotherapy room. After the evaluation, the researcher will open each participant’s envelope and see the random number that they have been assigned (without the knowledge of the participants or the outcome assessor). If the number assigned is between 1 and 40, the participant will be directed to the chemotherapy room on the east side of the hospital (intervention group); if the number is between 41 and 80, the participant will be directed to the chemotherapy room on the west side of the hospital (control group). We will for the participants in the intervention and control groups to be directed to different chemotherapy rooms, and a research assistant (RA) will accompany the participants to the rooms to minimise contamination of information between participants, between participants and intervention providers and between the nurses or doctors on duty.^42^

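### The repeated-measures analysis of anxiety, pain and vital signs pools three pre-intervention times with two post-intervention times, names no term, and so targets no S-VR versus control difference at T3 or T4

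*Protocol article*

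**What the plan says.** The Outcomes section sets five measurements of anxiety, pain, pulse and blood pressure: "thrice at pretest (baseline data collection, before the installation of intravenous access and before administration of VR intervention) and twice at post-test". Table 2 labels them T0 to T4.

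The Data analysis section assigns these outcomes to one method: "For anxiety, pain and vital-sign (blood pressure and pulse rate) outcome measurement analysis, General Linear Model-Repeated Measure (GLM-RM) statistics will be used". It describes that method as follows: "The GLM-RM is a statistical test used for the comparative analysis of two unpaired numerical data groups with more than two measurements". It excludes no time point and names no main effect, interaction or contrast. The fallback reads: "If the data are not normally distributed, the repeated Mann-Whitney alternative test with Bonferroni correction will be used". The number of comparisons to be corrected for is not given. The section lists seven confounders for adjustment (age, gender, education, cancer stage, chemotherapy cycle, assistance during chemotherapy, comorbidities). The outcome's own pre-intervention value is not among them.

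On timing, the Patient recruitment section says: "The participants will be evaluated (pretest) by the outcome assessor (research nurse) before they enter the chemotherapy room". The envelope is opened after that evaluation, and the two arms then go to chemotherapy rooms on different sides of the hospital.

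**The concern.** The secondary objectives ask what S-VR does to anxiety, pain and vital signs. Only T3 and T4 can show that. Yet the plan's description of GLM-RM requires more than two measurements. With two post-intervention times, that is met only if pre-intervention times enter as responses.

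Such a model offers two tests involving group, and neither is the wanted comparison. The main effect averages over three times at which the intervention cannot have acted. The group-by-time test asks whether the arm difference varies anywhere among five times. At stake are a missed effect under the first reading, and a significant result that cannot be placed at T3 or T4 under the second.

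**Working it through.** **The plan's own figure.** The Sample size calculation section gives effect size 0.81, two-sided alpha 5%, power 90% and 1:1 allocation. A noncentral t calculation gives power 0.8998 at 33 per group and 0.908 at 34, so 34 is right. Then 34/0.85 = 40 per group after 15% dropout. No effect size is given for anxiety, pain or vital signs.

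**Assumptions.** These are not in the document: effect d = 0.5 SD at both T3 and T4 and zero at T0 to T2; equal SDs; the same correlation r between any two times; n = 34 per arm.

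**Group main effect.**
- Raw difference: (0 + 0 + 0 + d + d)/5 = 0.4d = 0.20 SD.
- Variance of a five-time mean: (1 + 4r)/5. At r = 0.6 this is 0.68.
- Standardised effect: 0.20/√0.68 = 0.243; noncentrality 0.243 × √17; power 17%.

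**Group-by-time test.**
- Sum of squares of the pattern about its mean of 0.2: 3 × 0.2² + 2 × 0.3² = 0.30.
- Noncentrality (n/2) × 0.30/(1 − r) = 17 × 0.30/0.4 = 12.75, with 4 and 4 × 66 = 264 df; power 82%.

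**Mean of T3 and T4 adjusted for T0.**
- Residual variance: (1 + r)/2 − r² = 0.80 − 0.36 = 0.44.
- Standardised effect: 0.5/√0.44 = 0.754; power 86.5%.

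| Correlation | Main effect | Group-by-time | T0-adjusted T3/T4 mean |
|---|---|---|---|
| 0.4 | 20% | 63% | 79% |
| 0.6 | 17% | 82% | 86.5% |
| 0.7 | 15% | 92% | 92% |
| 0.8 | 14% | 99% | 98% |

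At the plan's d = 0.81 and correlations 0.3 to 0.8, the main effect has 51% down to 30% power. The group-by-time test has at least 95% and the T0-adjusted mean at least 99%.

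**Can T1 and T2 drive the group-by-time test?** Suppose the rooms or staff produce a 0.3 SD arm difference at T1 and T2 only, with none at T0, T3 or T4. The pattern mean is 0.12, and the sum of squares is 3 × 0.12² + 2 × 0.18² = 0.108. At r = 0.6 the noncentrality is 17 × 0.108/0.4 = 4.59, and the test is significant 36% of the time.

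**Bonferroni in the fallback.** Over five times the per-test alpha is 0.05/5 = 0.010; over two it is 0.05/2 = 0.025. At d = 0.5 and 34 per arm, per-test power (t-test as a guide) is 29% against 41%.

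**The case against.** The plan never says that the group main effect is the test. A reader might infer that the effect is diluted to 40% as a matter of fact. The document does not support that, because a group-by-time reading is equally open. Even under the main-effect reading, 40% is the raw difference. Averaging also reduces variance, so the standardised effect falls to between 60% and 44% of d at correlations 0.3 to 0.8. This objection stands.

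Keeping T0 to T2 as responses does not in itself cost power. A 1-df contrast of the post-intervention mean against the pre-intervention mean, within the same five-time model, has variance (1 − r)(1/2 + 1/3) = 0.333 at r = 0.6. Its power is 94%, above the T0-adjusted mean. This also stands, but the plan names no such contrast, and it would use T1 and T2 as baselines although they follow the opening of the envelope.

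Two further inferences go beyond the text. A five-fold Bonferroni correction is the natural reading of repeated tests over five times, but it is not stated. Losing patients with any missing time could also shrink the analysis set, but the document gives no missingness per time, so no size can be attached.

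Finally, a condensed article may leave the tested term to a statistical analysis plan. That answers a complaint about missing detail alone. It does not answer the rest: the article itself chooses the model, describes it so that pre-intervention times must be responses, and lists covariates without the baseline value.

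**Conclusion.** The point holds in conditional form. As described, the analysis does not target the arm difference at T3 and T4.

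- **If the main effect is read,** the raw effect is 40% of its true size (given equal effects at T3 and T4), and power is about 17% against 86.5% under the stated assumptions.
- **If the group-by-time test is read,** the power loss is modest at correlation 0.6, nil at 0.7 and above, and notable only at low correlation (63% against 79% at 0.4). The weakness is then interpretation: the omnibus test gives no difference at T3 or T4 and can respond to T1 or T2.

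That T1 and T2 follow room assignment rests on the order of events in Patient recruitment. T0 is the only measurement clearly placed before the envelope is opened. The size of any room effect is unknown; 0.3 SD is an illustration.

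The power figures rest on an assumed effect, equal SDs and a common correlation. Only secondary outcomes are concerned. Comfort, measured at T0 and T4 only, and the 34/40 sample size are untouched. The change is worth making but does not threaten the trial's main result.

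**What to change.** Amend the Data analysis section for anxiety, pain, pulse and blood pressure as follows.

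- Use T3 and T4 as the responses in a linear mixed model with arm, time and arm-by-time, adjusted for the T0 value of the same outcome.
- Report the arm difference with its 95% CI at T3 and at T4.
- Show T1 and T2 descriptively. A T2-adjusted model can serve as a sensitivity analysis.
- State the number of comparisons, and limit any Bonferroni correction to T3 and T4, in the Mann-Whitney fallback as well as the main model.

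The cost is wording only. T0 is already collected, no visit or measurement is added, and SPSS has a mixed-model procedure.
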